#### 4.4.1. Anticancer Treatment

If a subject requires additional anticancer treatment (e.g., chemotherapy, radiation therapy, or surgery), he or she will not be able to continue with GSK1363089 treatment and will enter the Post-Treatment Period (end-of-treatment visit/follow-up). Palliative radiotherapy is allowed during the study only in the event that the lesion to be radiated

was recognized prior to study entry, and neither the presence of the lesion nor the need for its radiation represent PD.

#### **4.4.2. Supportive Care**

Antiemetics and antidiarrheal medications will not be administered prophylactically before initial treatment with study drug. At the discretion of the investigator, prophylactic use of antiemetic and antidiarrheal medication may be used as per standard clinical practice before subsequent doses of study drug.

Colony-stimulating factors (e.g., erythropoietin and granulocyte colony stimulating factor) and pain medications administered as dictated by standard clinical practice are acceptable while the subject is enrolled in the study.

#### **4.4.3. Management of Treatment-Emergent Hypertension**

Subjects may develop hypertension as a result of GSK1363089 treatment. It is recommended that hypertension is addressed prior to treatment initiation. [Table 2](#) provides a recommended algorithm for hypertension management. Decisions to hold or decrease the GSK1363089 dose during treatment must be based on BP readings taken by a medical professional and must be confirmed with a second measurement at least 5 minutes following the first measurement. While subjects are receiving treatment with GSK1363089, the early initiation of antihypertensive treatment for Grade 1 or 2 hypertension to minimize more severe or persistent hypertension is not considered a Grade 3 AE.

**Table 2 Management of Treatment-Emergent Hypertension**

| BP Measurements - Systolic/Diastolic                                                                                             | Treatment/Dose Modification                                                                                                                                                                                                                                                                                                                                              |
|----------------------------------------------------------------------------------------------------------------------------------|--------------------------------------------------------------------------------------------------------------------------------------------------------------------------------------------------------------------------------------------------------------------------------------------------------------------------------------------------------------------------|
| Subjects not receiving maximal antihypertensive therapya                                                       |                                                                                                                                                                                                                                                                                                                                                                          |
| >140 mmHg (systolic)
OR
>90 mmHg (diastolic)
OR
Increase of diastolic BP by $\geq 20$ mmHg regardless of baseline BP | 
 
• Add new or additional antihypertensive medications or increase dose of existing medications.
 
• Maintain dose of GSK1363089.
 
                                                                                                                                                                                 |
| >180 mmHg (systolic)
OR
>105 mmHg (diastolic)                                                                              | 
 
• Hold GSK1363089.
 
• Add new or additional antihypertensive medications or increase dose of existing medications.
 
• Monitor subject closely for hypotension (if on antihypertensive meds) until GSK1363089 is restarted.
 
• Resume treatment at same dose level when BP falls to <140/90.
 
 |
| Subjects receiving maximal antihypertensive therapya                                                           |                                                                                                                                                                                                                                                                                                                                                                          |
| >160 mmHg (systolic)
OR
>105 mmHg (diastolic)                                                                              | 
 
• Hold GSK1363089.
 
• Maintain antihypertensive medications and monitor subject closely for hypotension until GSK1363089 is restarted.
 
• Resume treatment at one lower dose level when BP falls to <140/90 (see Section 3.4 for details of dose reduction).
 
                                        |

a Maximal antihypertensive therapy is defined as four antihypertensive medications given for 2 weeks.

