### 3.4. Dose Reduction or Treatment Delay for Toxicity

For the purpose of this protocol and for assistance with making decisions regarding dose reduction or delays, the following CTCAE Grade 3 definitions have been slightly modified (modifications are in italics):

- Grade 3 hypertension *despite optimal antihypertensive therapy with one or more drugs* (see [Management of Treatment-Emergent Hypertension](#) for information regarding management of treatment-emergent hypertension)
- Grade 3 nausea, vomiting, or diarrhea *despite prophylaxis and/or treatment* (see Section [4.4.2](#) for information regarding supportive care treatment)

In the event of treatment emergent hepatotoxicity, irrespective of whether the investigator considers it related to study drug, the management guidelines described in Section [4.4.4](#) should be followed.

If a subject experiences a new onset of unacceptable symptoms or signs of toxicity (excluding hepatotoxicity which is covered above), but in the investigator's opinion should continue to receive study drug, study treatment may be delayed for up to 21 days, then resumed either at the same dose or at a reduced dose, according to the criteria set out in Sections [3.4.1](#) and [3.4.2](#). The details of how to dose-reduce subjects are set out in Sections [3.4.3](#) and [3.4.4](#).

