#### 3.4.1. Symptoms/Signs Unrelated to Study Drug

If unacceptable symptoms or signs of toxicity are considered unrelated to study drug and resolve within 21 days, the subject may resume study treatment at his or her current dose level.

If unacceptable symptoms or signs of toxicity are considered unrelated to GSK1363089 but have not resolved to Grade  $\leq 1$  or to within 10% of baseline values within 21 days, the subject will receive no further doses of GSK1363089 and will enter the Post-Treatment Period.

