#### 3.4.2. Symptoms/Signs Related to Study Drug

If unacceptable study drug-related symptoms resolve within 21 days, the subject may resume study treatment with a reduction in dose.

If, after 21 days, study drug-related symptoms or signs of toxicity do not resolve to Grade  $\leq 1$  or to within 10% of baseline values, the subject will receive no further doses of GSK1363089 and will enter the Post-Treatment Period.

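### For drug-related hypertension on optimal but sub-maximal antihypertensive therapy, Table 2 and Section 3.4.2 give different restart doses, and no text says which governs

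*Combined protocol and SAP*

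**What the plan says.** **Section 3.4** modifies some Grade 3 definitions to help with decisions on dose reduction and delay. Hypertension is one of them: it counts when Grade 3 persists "despite optimal antihypertensive therapy with one or more drugs", with a pointer to the hypertension section. For a new unacceptable toxicity, treatment may be delayed for up to 21 days and then restarted under Section 3.4.1 or 3.4.2. Hepatotoxicity is the only toxicity excluded from this rule.

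**Sections 3.4.1 and 3.4.2** divide by relatedness. After an unrelated event that resolves, "the subject may resume study treatment at his or her current dose level". After a drug-related event that resolves within 21 days, "the subject may resume study treatment with a reduction in dose". A related event that has not come down to Grade 1 or below, or to within 10% of baseline, after 21 days ends treatment.

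**Section 4.4.3** covers drug-induced hypertension expressly ("Subjects may develop hypertension as a result of GSK1363089 treatment"), and its Table 2 "provides a recommended algorithm for hypertension management". Table 2 divides subjects by intensity of antihypertensive therapy: "Maximal antihypertensive therapy is defined as four antihypertensive medications given for 2 weeks". It has two rows that hold study drug:
- Not on maximal therapy, above 180 systolic or 105 diastolic: hold, intensify antihypertensives, then "Resume treatment at same dose level when BP falls to" 140/90.
- On maximal therapy, above 160 systolic or 105 diastolic: hold, then "Resume treatment at one lower dose level when BP falls to" 140/90, with a reference to Section 3.4 for the dose steps.

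**The concern.** The two passages sort the same event on different axes. Section 3.4 asks whether the event is drug-related. Table 2 asks whether the subject is on four antihypertensives for 2 weeks. Between *optimal therapy with one or more drugs* and *maximal therapy* lies a group that both passages address, with different restart doses.

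Safety and tolerability form a primary objective (Section 2), and comparing the two regimens is an exploratory one. With up to 20 sites (Section 3.2), the same event could be handled as a dose reduction at one site and not at another. Reductions, dose intensity and discontinuations for hypertension would then partly reflect which passage a site followed. Each subject's dose would depend on the same accident.

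**Working it through.** The plan gives no figure to reproduce. The check sets the passages side by side for drug-related hypertension with study drug held.

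| Antihypertensive therapy at the event | Table 2 restart | Section 3.4.2 restart | Result |
|---|---|---|---|
| (a) Maximal; >160 or >105 mmHg | One level lower | Reduced | Agree |
| (b) Optimal with one to three drugs, or four for under 2 weeks; >180 or >105 mmHg; event judged unacceptable | Same level | Reduced | Conflict |
| (c) Not yet optimal; >180 or >105 mmHg | Same level | Applies only if the event is judged unacceptable | Conflict possible, not forced |

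**Restart conditions**
- Table 2: blood pressure below 140/90, no time limit.
- Section 3.4.2: Grade 1 or below, or within 10% of baseline, by 21 days; otherwise no further study drug.
- A subject who has met neither target after day 21 stays on hold under Table 2 and ends treatment under Section 3.4.2.

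**Size of the dose difference**, for a first reduction from the starting dose (Sections 3.4.3 and 3.4.4)
- Cohort 1: (240 − 160)/240 = 33%.
- Cohort 2: (80 − 60)/80 = 25%.

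**Frequency of severe related hypertension in earlier studies**
- XL880-001 (Section 1.3.3.3.1): 2 of 40 = 5.0%.
- XL880-002 (Section 1.3.3.3.2): 1 of 24 = 4.2%.
- MET111644 (Section 1.3.3.3.3): 3 of 16 = 18.75%.
- Pooled: (2 + 1 + 3)/(40 + 24 + 16) = 6/80 = 7.5%.
- At 7.5%, a cohort of 30 to 40 would have about 30 × 0.075 = 2.25 to 40 × 0.075 = 3 such subjects.

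This is a guide to order of magnitude, not an estimate of row (b). Only some Grade 3 events would fall in that row, and the row is entered on blood pressure and clinical judgement, not on grade alone. The earlier studies also used other doses: the XL880-002 case arose at 120 mg/day (Sections 1.3.3.3.2 and 5.11), above Cohort 2's 80 mg.

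**The case against.** The best defence is that Table 2 is the specific rule and Section 3.4 only supplies the dose steps. The hypertension item in Section 3.4 points to the hypertension section. Section 5.1 refers to Section 3.4 for delays and reductions, and separately to Section 4.4.3 for drug-related hypertension. Table 2 refers back to Section 3.4 only in its reducing row, and only for how to reduce. Read this way there is one sequence: intensify antihypertensives first, and lower study drug once they are maximal. A subject whose antihypertensives can still be increased is arguably not yet on optimal therapy, which would shrink row (b). Neither text is strictly mandatory either: Table 2 is a recommendation and Section 3.4.2 says *may*.

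Much of this stands. Table 2 taking precedence is a plausible intent, and row (c) is not a forced conflict. But no sentence gives Table 2 precedence. Section 3.4 shows how a toxicity is carved out, does so for hepatotoxicity, and instead lists hypertension among the inputs to its own decisions. The pointers offer information, and Section 5.1 names both sections side by side without ranking them. Calling Table 2 a recommendation weakens its claim to override. The *may* in Section 3.4.2 permits restarting with a reduction; next to the current-dose wording of Section 3.4.1, it is not naturally read as also allowing the same dose.

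**Conclusion.** The conflict is real but confined to row (b): study drug held under Table 2's sub-maximal row, therapy already optimal, event drug-related and judged unacceptable. There the passages differ by one dose level (33% in Cohort 1, 25% in Cohort 2, at a first reduction) and in their restart and time-limit conditions. This should be corrected, because it lets sites dose the same event differently in a trial with tolerability as a primary objective.

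The conclusion assumes that *optimal* therapy can be reached short of four drugs for 2 weeks. The phrase *one or more drugs* supports that, but the protocol does not define the term.

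A reader might infer more in three ways, and the documents do not support any of them:
- That Table 2 contradicts Section 3.4.2 for all severe drug-related hypertension. Its maximal-therapy row lowers the dose and agrees.
- That the conflict reaches the 42% with related hypertension or increased blood pressure in Section 5.11. That list is not limited to severe events or to events needing a hold. The size of the affected group cannot be derived from the documents.
- That the tolerability results or the regimen comparison would be invalid. No such effect can be estimated, and the comparison is exploratory and non-randomized in any case.

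**What to change.** Reconcile Sections 3.4 and 3.4.2 with Table 2 in the next amendment:
1. State which passage governs treatment-emergent hypertension. If it is Table 2, add hypertension to the exclusion in Section 3.4 next to hepatotoxicity; if it is Section 3.4.2, amend the sub-maximal row of Table 2 to match.
2. Use one defined description of antihypertensive therapy in both places, or define *optimal* and state how it relates to *maximal*.
3. Align the blood pressure and grade conditions for restarting, and say whether the 21-day limit applies to a hypertension hold.

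Which dose rule, threshold or limit to adopt is for the sponsor's physicians; this review takes no position. The cost is clarifying wording and notice to sites, with no change to sample size or analysis.

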#### 4.4.4. Management of Treatment-Emergent Hepatotoxicity

In the event of treatment-emergent hepatotoxicity, potential contributing factors such as concomitant medications, viral hepatitis, choledocholithiasis, and hepatic metastases should be investigated. Concomitant medications known to be hepatotoxic which may be contributing to liver dysfunction should be discontinued or replaced with alternative medications to allow for recovery of liver function. As generally understood, ALT  $>3$  x ULN and concomitant bilirubin  $\geq 2.0$  x ULN ( $>35\%$  direct bilirubin), in the absence of elevated alkaline phosphatase or biliary injury, suggests significant liver injury.

Table 3 shows the liver-enzyme entry criteria, split by whether there is liver involvement.

**Table 3 Liver Enzyme Entry Criteria**

|                        | No liver involvement                                     | With liver involvement                               |
|------------------------|----------------------------------------------------------|------------------------------------------------------|
| ALT and AST     | $\leq 2.5 \times \text{ULN}$                             | $\leq 5 \times \text{ULN}$                           |
| Total bilirubin | $\leq 1.5 \text{ mg/dL}$ or $\leq 1.5 \times \text{ULN}$ | $\leq 2 \text{ mg/dL}$ or $\leq 2 \times \text{ULN}$ |

Liver chemistry stopping and follow-up criteria have been designed to ensure subject safety and evaluate liver event etiology. [Appendix G](#) provides a flow diagram of these criteria.

Therapy with GSK1363089 should be terminated if any of the following criteria are met:

11. ALT  $\geq 3 \times \text{ULN}$  or  $\geq 3 \times \text{Baseline}$  (if baseline ALT  $> \text{ULN}$ ) **and** bilirubin  $\geq 1.5 \times \text{ULN}$  or  $\geq 1.5 \times \text{Baseline}$  (if baseline bilirubin  $> \text{ULN}$  **and**  $> 35\%$  direct bilirubin)
12. ALT  $\geq 5 \times \text{ULN}$  or  $\geq 5 \times \text{Baseline}$  (if baseline ALT  $> \text{ULN}$ )
13. ALT  $\geq 3 \times \text{ULN}$  or  $\geq 3 \times \text{Baseline}$  (if baseline ALT  $> \text{ULN}$ ) if associated with the appearance or worsening of hepatitis symptoms
14. ALT  $\geq 3 \times \text{ULN}$  or  $\geq 3 \times \text{Baseline}$  (if baseline ALT  $> \text{ULN}$ ) that persists for  $\geq 4$  weeks

Baseline ALT and total bilirubin should be calculated as the average of **all** liver chemistry results obtained from Screening through Day 1. This requirement is based on the variability of baseline and screening ALT values observed in an earlier study.

**When any of the liver chemistry stopping criteria is met, do the following:**

- **Immediately withdraw GSK1363089**
- Report the event to GSK within **24 hours** of learning its occurrence
- Complete the liver event CRF
- Complete the SAE data collection tool if the event also meets the criteria for an SAE
- Perform liver imaging (CT scan or MRI) within 7 days
- Complete the liver imaging and/or liver biopsy CRFs if these tests are performed
- Perform liver event follow-up assessments, and monitor the subject until liver chemistries resolve, stabilize, or return to baseline values as described below
- Withdraw the subject from the study after completion of the liver chemistry and viral studies and resolution of liver function to baseline levels
- Do not rechallenge with investigational product

In addition, for criterion 1:

- Make every reasonable attempt to have subjects return to clinic within **24 hours** for repeat liver chemistries, liver event follow-up assessments (see below), and close monitoring
- A specialist or hepatology consultation is recommended
- Monitor subjects twice weekly until liver chemistries (ALT, AST, alkaline phosphatase, bilirubin), complete blood count, platelet count, and prothrombin time resolve, stabilize or return to within baseline values
- Measure anti-nuclear antibody, anti-smooth muscle antibody, and Type 1 anti-liver-kidney microsomal antibodies
- Liver biopsy may be performed at the discretion of the investigator

For all other criteria:

- Make every reasonable attempt to have subjects return to clinic **within 24 to 72 hours** for repeat liver chemistries and liver event follow-up assessments (see below)
- Monitor subjects weekly until liver chemistries (ALT, AST, alkaline phosphatase, bilirubin) resolve, stabilize or return to within baseline values

Subjects with ALT  $\geq 3 \times \text{ULN}$  **but**  $< 5 \times \text{ULN}$  or  $\geq 3 \times \text{Baseline}$  (if baseline ALT  $> \text{ULN}$ ) **but**  $< 5 \times \text{Baseline}$  (if baseline ALT  $> \text{ULN}$ ) **and** bilirubin  $< 1.5 \times \text{ULN}$  or  $< 1.5 \times \text{Baseline}$  (if baseline bilirubin  $> \text{ULN}$ ), without hepatitis symptoms or rash, and who can be monitored weekly for 4 weeks:

- Can continue investigational product
- Must return weekly for repeat liver chemistries (ALT, AST, alkaline phosphatase, bilirubin), complete blood count, platelet count, and prothrombin time until they resolve, stabilize or return to within baseline values
- If at any time these subjects meet the liver chemistry stopping criteria, proceed as described above
- If, after 4 weeks of monitoring, ALT  $< 3 \times \text{ULN}$  **or**  $< 3 \times \text{Baseline}$  (if baseline ALT  $\geq \text{ULN}$ ) and bilirubin  $< 1.5 \times \text{ULN}$  **or**  $< 1.5 \times \text{Baseline}$  (if baseline bilirubin  $> \text{ULN}$ ), monitor subjects twice monthly until liver chemistries normalize or return to within baseline values

If any of the stopping criteria is met, make every attempt to carry out the **liver event follow-up assessments** described below:

- Viral hepatitis serology including:  
Hepatitis A immunoglobulin M (IgM) antibody

Hepatitis B surface antigen and hepatitis B core antibody (IgM)

Hepatitis C RNA

Cytomegalovirus IgM antibody

Epstein-Barr viral capsid antigen IgM antibody (or if unavailable, obtain heterophile antibody or monospot testing)

Hepatitis E IgM antibody (if subject resides outside the United States or Canada, or has traveled outside United States or Canada in past 3 months)

- Blood sample (3 mL) for PK analysis, obtained within 72 hours (preferably within 24 hours) of last dose. Record the date/time of the PK blood sample draw and the date/time and amount of the last dose of investigational product before blood sample draw on the CRF. If the date or time of the last dose is unclear, provide the subject's best approximation. If the date/time of the last dose cannot be approximated OR a PK sample cannot be collected in the time period indicated above, do not obtain a PK sample. Instructions for sample handling and shipping are in the PK Laboratory Manual.
- Serum creatine phosphokinase and LDH
- Obtain complete blood count with differential to assess eosinophilia
- Record the appearance or worsening of clinical symptoms of hepatitis, or hypersensitivity, fatigue, decreased appetite, nausea, vomiting, abdominal pain, jaundice, fever, or rash as relevant on the AE CRF
- Record use of concomitant medications, acetaminophen, herbal remedies, other over-the-counter medications, or putative hepatotoxins, on the concomitant medications CRF
- Record alcohol use on the liver event alcohol intake CRF

#### 4.5. Potential Drug Interactions

Drug interaction studies have not been conducted with GSK1363089 in humans. However, *in vitro* studies indicate NADPH-dependent liver microsomal oxidative metabolism of GSK1363089 by CYP3A4. Therefore, use of drugs that are inhibitors or inducers of CYP3A4 should be avoided in subjects who are receiving GSK1363089 (e.g., 3A4 inhibitors ketoconazole, HIV protease inhibitors, diltiazem, and verapamil and 3A4 inducers phenobarbital, phenytoin, and rifampin).

*In vitro*, GSK1363089 is a moderate inhibitor of hepatic microsomal isozymes cytochrome P450 (CYP): CYP3A4, CYP2C8, CYP2C9, and CYP2D6. Therefore, use of drugs that are substrates of the liver enzymes CYP3A4 (e.g., triazolobenzo-diazepines, dihydropyridine calcium channel blockers, certain HMG-CoA reductase inhibitors),

CYP2D6 (e.g., tricyclic antidepressants, venlafaxine, fluoxetine, paroxetine, beta blockers, and codeine), CYP2C8 (e.g., repaglinide, cerivastatin, torsemide), and CYP2C9 (e.g., phenytoin, warfarin, and non-steroidal anti-inflammatory drugs) should be avoided in subjects who are receiving GSK1363089 unless deemed clinically necessary (i.e. no non-P450 interacting alternative is available) and the subject can be monitored for the desired drug effect or level and for potential adverse effects. See [Appendix D](#) for a more comprehensive list of drugs that inhibit/induce CYP3A4, or are a substrate for CYP3A4, CYP2D6, CYP2C8, or CYP2C9.

GSK1363089 is highly protein bound, and other drugs that are also highly protein bound should be used with caution and may require more frequent monitoring of effects. Examples of such agents include warfarin, diazepam, furosemide, dicloxacillin, propranolol, and phenytoin.

